#### Body composition

Body composition during fish oil/corn oil intake is measured by a bioimpedance scale. A small electrical impulse (approx. 0.8 mA) is released to the skin in contact with the surface of the scale. Different conductivities and resistances in different tissue types make it possible to calculate body mass index, and the percentage of fat and muscle tissue, respectively. The measurement will be carried out at baseline, prior to each chemotherapy session and at 8 months (visits 1, 2, 3, 4 and 5) [60, 61].

#### Cognitive evaluation

Cognitive evaluation will be carried out at baseline and at 8 months (visits 1 and 5). The tests comprise the trail making test A+B and part of the EORTC-QLQC30 questionnaire concerning cognition. In test A the patient must draw lines to connect circled numbers in a numerical sequence (1-2-3, etc.) as rapidly as possible. In test B the patient must draw lines to connect circled numbers and letters in an alternating numeric and alphabetic sequence (1-A-2-B, etc.) as rapidly as possible. Test scores (finishing time) are compared with normative data stratified by age [62].

#### Documentation of cardiac events

To establish whether a cardiac or thromboembolic event has taken place during the trial period, patients are asked at visit 5. The statement is verified by a specific search in the patient's medical record during the trial period. The search words are “cardiac event”, “AMI”, “STEMI”, “thromboembolic VTE”, and “LE”.

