#### Quality of life

Quality of life based on the EORTC QLQ 30 questionnaire at each visit compared to baseline. EORTC QLQ-30 is a self-reported questionnaire assessing the health-related quality of life (HRQoL) of cancer patients in clinical trials. The questionnaire is divided into three subscales assessing global health status, functional scales (physical functioning, role functioning, emotional functioning, cognitive functioning, and social functioning) and symptom scales/items (fatigue, nausea and vomiting, pain, dyspnea, insomnia, appetite loss, constipation, diarrhea, and financial difficulties). HRQoL will be evaluated using the QLQ-C30 at baseline and at each planned visit until the end of the study (visits 1, 2, 3, 4 and 5). The scores will be calculated according to the standard operating procedure of the EORTC and rated from 0 to 100.

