#### Assessment of adverse events

Adverse events will be assessed by the EORTC-QLQ 30 at visits 2, 3, and 4 and by open-ended questions at visit 5.

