### Statistical analysis and sample size

The present study will compare the treatment outcomes of patients in the two arms.

Based on previous studies we expect an OIPN prevalence of 50% in the control group and estimate a prevalence in the fish oil group to be 23%, which is a clinically meaningful difference [6, 39, 63]. Using 80% power and 5% risk of type I error, the sample size estimate is 49+49 patients for the primary objective. To account for dropouts, the project will include 120 patients, with 60 patients in each group.

Patient demographics and baseline characteristics will be described using descriptive statistics. Continuous variables will be summarized according to their distribution with medians and interquartile range (IQR) or means and standard deviations (sd). Categorical variables will be summarized with frequencies and percentages.

The primary endpoint (OIPN) is a dichotomous endpoint defined by the developed definition of OIPN. The two independent proportions of OIPN in the two randomization arms will be compared using the chi^2^ test and reported as frequencies and percentages with corresponding p-values. P-values <0.05 will be considered statistically significant. All analyses will be performed as intention-to-treat (ITT). In case of cross-over between study arms due to non-compliance, per protocol analyses will be performed as sensitivity analyses to explore the potential bias from the non-compliance. In per-protocol analyses, non-compliance will be defined using an 80% percent cut-off or a significant lack of DHA and EPA rise in compliance blood samples.

The proportion and patterns of missing data will be explored, and in the case of <5% missing data, analyses will be performed as complete case. If the amount of missing data is comprehensive (>5%) or suggestive of biased estimates, appropriate methods of imputation will be applied depending on the patterns of missingness.

A complete statistical analysis plan covering each outcome will be developed together with statistical consultant [name] M.Sc., PhD. Statistical analyses will be performed using STATA version 18 (STATA Corp., Texas, USA) and all steps of data management, coding and analyses will be logged.

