### Ethical considerations

The trial does not affect the treatment regimen or follow-up for the patients. Skin biopsies are minimally invasive. It may cause a short lasting discomfort when placing the local anesthetic, and a small risk of wound infection (1:1.000). The risks involved in blood sampling include a small risk of temporary soreness and hematoma at the point of perforation.

Patients will not be financially reimbursed or compensated.

OIPN is a serious complication with no treatment options. Fish oil and corn oil have no known adverse effects. The group of patients receiving fish oil may benefit from reduced neuropathy caused by the standard chemotherapy.

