Despite our attempt to address study limitations by adhering to the ACTTION guidelines on CIPN trials [57], we acknowledge several limitations. The duration of the trial and the number of invasive prcodures (skin biopsy and blood samples) can be limitations due to the risk of discontinuations and subsequent inadequate power. Furthermore, power calculations were based on primary outcome only, thereby raising concerns of power for the secondary and tertiary outcomes, which consequently will be regarded as exploratory only.

Since OIPN and neuropathic pain are not manageable or preventable, the current situation in oncology departments today is that OIPN and associated neuropathic pain cause dose reduction and premature cessation of potential lifesaving chemotherapy.

In this study we aim both to explore the mechanisms behind OIPN, evaluate different potential predictive biomarkers and we examine a potential preventive treatment with a robust design. The main goal is to increase quality of life in cancer survivors receiving neurotoxic chemotherapy and potentially optimize treatment with oxaliplatin without invalidating side-effects.

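### The five-word record search that verifies cardiac and thromboembolic events is narrower than the endpoint it is meant to verify

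*Protocol article*

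**What the plan says.** Under Documentation of cardiac events, among the tertiary endpoints, the protocol article describes two steps. The patient is asked first: "To establish whether a cardiac or thromboembolic event has taken place during the trial period, patients are asked at visit 5". The answer is then checked: "The statement is verified by a specific search in the patient's medical record during the trial period". The check is fixed by a list: "The search words are “cardiac event”, “AMI”, “STEMI”, “thromboembolic VTE”, and “LE". The section gives no other terms and no diagnosis codes, and it does not say which event types count. The article's abbreviation list does not expand AMI, STEMI, VTE or LE.

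Three other places bear on the point:

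- The section on adverse event assessment, which sets the general safety capture: "Adverse events will be assessed by the EORTC-QLQ 30 at visits 2, 3, and 4 and by open-ended questions at visit 5".
- Quality of life, which lists that questionnaire's symptom scales and items: "fatigue, nausea and vomiting, pain, dyspnea, insomnia, appetite loss, constipation, diarrhea, and financial difficulties".
- Discussion, on the standing of endpoints below the primary one: "raising concerns of power for the secondary and tertiary outcomes, which consequently will be regarded as exploratory only".

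**The concern.** The endpoint is a broad class of events, while its verification is a closed list of five terms. One is a generic phrase (*cardiac event*), two are infarction abbreviations (*AMI*, *STEMI*), one is a compound (*thromboembolic VTE*), and one is the unexpanded *LE*. A check that has no word for some parts of its endpoint cannot confirm them. It also cannot correct a patient who forgets or does not recognise such an event.

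This is the only specific cardiovascular safety measure that the article describes. The Discussion calls the fish oil dose significantly higher than in comparable studies, and Ethical considerations states: "Fish oil and corn oil have no known adverse effects". With 120 patients followed for 8 months, few events are likely, so the reliability of each record matters to any descriptive safety statement.

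This is not detail that an article leaves to a fuller document. The list is stated, and it does not fit the endpoint named in the same section.

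**Working it through.** **1. Inputs.** The endpoint, the two-step procedure and the five terms come from Documentation of cardiac events. The article gives no numerical figure for this endpoint, so there is nothing to reproduce. Its only assumed outcome rates concern the primary endpoint ("we expect an OIPN prevalence of 50% in the control group and estimate a prevalence in the fish oil group to be 23" per cent) and play no part here.

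**2. Match of event names against the list.** The article does not say how the search is run, so each name was tested under three readings: whole word or phrase, substring, and *thromboembolic VTE* split into two words.

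| Name as written in a note | Whole word or phrase | Substring | Compound split |
|---|---|---|---|
| AMI; STEMI; LE | hit | hit | hit |
| NSTEMI | none | hit (through STEMI) | none |
| VTE | none | none | hit |
| myocardial infarction; pulmonary embolism; venous thromboembolism (in full) | none | none | none |
| deep vein thrombosis; DVT | none | none | none |
| arrhythmia; atrial fibrillation; heart failure; angina | none | none | none |
| stroke | none | none | none |

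Arrhythmia, heart failure and angina have no term under any reading. They could surface only if a note happened to use the generic phrase *cardiac event* or another listed term. Deep vein thrombosis has one route: the note must say VTE and the compound must be split.

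**3. What follows for a patient seen at visit 5.** Take an event of a type without a term.

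- Reported by the patient: it is known from the patient's answer, but the specified search does not confirm it.
- Not reported: the specified search does not pick it up.

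**4. Other sources.** The questionnaire used at visits 2 to 4 has no cardiac or thromboembolic item among the symptom scales listed; dyspnea is the nearest. The open-ended questions at visit 5 again depend on the patient's recall. The record search is therefore the only source described for these events that does not rest on the patient's account.

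**5. Size.** Suppose *K* events occur and a share *u* is of types without a term. The search can then confirm at most *K*(1 − *u*). The article gives neither *K* nor *u*. Over the full range of *u* from 0 to 1, the bound runs from all events to none. A chosen value of *u* would only return itself as the share unconfirmed, so no figure is offered.

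**The case against.** The strongest reply is that the search is the second source and not the first. Patients are asked directly, and open-ended adverse event questions are put at the same visit. Nothing in the article says that an unconfirmed report is discarded. This stands. A reader might infer that the trial will lose most of these events, or could find no excess simply because its instrument cannot see them. The documents do not support either inference: a reported event is unconfirmed rather than lost, and *most* has no figure behind it.

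Other parts of the reply also stand:

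- VTE is on the list, so a thrombosis noted that way may be found.
- The article does not say whether stroke belongs to the endpoint, so it cannot be counted as an omission.
- It is tempting to argue that English phrases will not occur in Danish hospital notes. The sites are Danish, but the article is in English and may have translated its terms, so this remains inference.
- The outcome is exploratory. The Discussion cites a study of almost 26,000 patients with no excess of cardiovascular events, and 60 patients per arm would not settle the question however good the search.

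What the reply does not remove is the mismatch itself. The list is given as the definition of the search, and translating the five terms would not add one for arrhythmia, heart failure or angina.

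**Conclusion.** The point holds as a mismatch between a stated verification rule and its own endpoint. For arrhythmia, heart failure and angina, and for deep vein thrombosis outside one reading, the specified search neither confirms a reported event nor detects an unreported one. This rests on two assumptions: that the five terms are applied as listed, and that the endpoint is as wide as its wording. If the sponsor meant only infarction and venous thromboembolism, the endpoint wording is too broad. Full names such as pulmonary embolism and myocardial infarction would still not match.

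The number of events affected is unknown and cannot be derived from the document. The consequence is confined to an exploratory safety outcome. The correction is worth making because it is cheap and concerns the only specific cardiovascular safety measure described.

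**What to change.** 1. State which event types count, including whether arterial events such as stroke do.
2. Replace the five-word list with diagnosis codes plus free-text terms and usual abbreviations for those types, in the language of the record.
3. Run the search over the whole trial period for every randomized patient, whatever was reported at visit 5. This includes patients who never reach that visit and so have no statement to verify.
4. Complete the search before unblinding, which already follows data analysis under Randomization and blinding. Report events by type and arm as an exploratory safety outcome.

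The cost is a wider query in records that are already being searched and a few more hits to read per patient. No visit or procedure is added, and the same search can be run over the trial period of patients already enrolled.

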#### Assessment of blinding

At the end of the trial (visit 5), the patient and investigator will be asked which treatment they think the patient has received and the reason for this.

#### Assessment of adverse events

Adverse events will be assessed by the EORTC-QLQ 30 at visits 2, 3, and 4 and by open-ended questions at visit 5.

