### Design and methods

Project OxaNeuro is an investigator-initiated, multicenter, double blinded, randomized placebo-controlled clinical trial. Patients are randomized to one of two arms: fish oil capsules or identical corn oil capsules for 8 months in total.

The study comprises daily intake of capsules, six visits, neurological and sensory examination, questionnaires, skin biopsies and blood sampling. Five of the six visits are scheduled together with planned visits at the Department of Oncology. Adjuvant chemotherapy is concluded after visit four, but the patients will continue with the daily intake of the trial supplements for a total of 8 months. During the follow-up period, patients will receive two phone calls to monitor compliance. The last visit (visit 5) is planned after 8 months, and this concludes the trial period (Fig. 1).

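### Until month 8 adverse events are read from a quality-of-life form, and the cardiac and thromboembolic record search is tied to a visit 5 statement, leaving patients without visit 5 no stated route of capture

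*Protocol article*

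**What the plan says.** Four parts of the protocol article bear on this.

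- **Assessment of adverse events.** The whole stated procedure is: "Adverse events will be assessed by the EORTC-QLQ 30 at visits 2, 3, and 4 and by open-ended questions at visit 5".
- **Quality of life.** The instrument is described in these terms: "EORTC QLQ-30 is a self-reported questionnaire assessing the health-related quality of life (HRQoL) of cancer patients in clinical trials". It has a global health scale, five functional scales, and "symptom scales/items (fatigue, nausea and vomiting, pain, dyspnea, insomnia, appetite loss, constipation, diarrhea, and financial difficulties". It is also listed as a tertiary endpoint.
- **Documentation of cardiac events.** An interview comes first: "To establish whether a cardiac or thromboembolic event has taken place during the trial period, patients are asked at visit 5". This is followed by a check: "The statement is verified by a specific search in the patient's medical record during the trial period". Search terms follow.
- **Design and methods.** On timing: "The last visit (visit 5) is planned after 8 months, and this concludes the trial period". Chemotherapy ends after visit 4, while capsules continue to 8 months. The two phone calls in follow-up are there to monitor compliance; the Compliance section adds retention. Neither section gives them a safety purpose.

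Two other sections show who may not reach visit 5. Study population and eligibility withdraws patients with verified relapse. The Discussion names discontinuation as a limitation.

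**The concern.** A closed list can record only what it names. Dyspnea or pain might be a symptom of a cardiac or thrombotic event, but a scale score does not identify the event, its date or its seriousness. The first open question comes at 8 months, when an untargeted event during chemotherapy has to be recalled over several months.

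The second problem is that safety data depend on attendance. If the cardiac and thromboembolic search starts from a visit 5 statement, an event that kills the patient or leads to withdrawal can remove the occasion on which it would have been found. Such a loss is not random. If attendance at visit 5 also differs between arms, the comparison of event rates is biased, in a direction that cannot be known in advance.

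At stake is what the trial can say about tolerability. The Discussion describes the fish oil dosage as well above that of comparable studies, and it is given alongside chemotherapy. The plan gives cardiac and thromboembolic events a section of their own, so complete capture serves its own purpose. The Statistical analysis section says all analyses are intention-to-treat; a safety comparison confined to visit 5 attenders would not be.

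**Working it through.** **Step 1. What each contact can capture, as the article states it**

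| Contact | Stated adverse-event tool | Bleeding, infection, allergy, rash | Cardiac or thromboembolic event |
|---|---|---|---|
| Visits 2, 3, 4 | QLQ-C30 | No item | No item |
| Two phone calls | None (compliance, retention) | None stated | None stated |
| Visit 5 | Open-ended questions; cardiac interview plus record search | Yes, by recall | Yes, checked in the record |
| Death or withdrawal before visit 5 | None stated beyond forms already completed | None stated | None stated |

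The last row is the gap. The search period covers the whole trial, but the search is worded as verification of a statement. Without visit 5 there is no statement to verify. The wording also leaves open whether a patient who answers no is searched.

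**Step 2. How many patients could lack visit 5**

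The article gives no forecast. The only related figure is the dropout allowance, so the sample size behind it is reproduced first.

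Inputs (Statistical analysis and sample size): p1 = 0.50, p2 = 0.23, power 80%, type I error 5%. Sidedness is not stated; two-sided is assumed.

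n per arm = [z(0.975) × √(2 p̄(1 − p̄)) + z(0.80) × √(p1(1 − p1) + p2(1 − p2))]² / (p1 − p2)²

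- p̄ = (0.50 + 0.23)/2 = 0.365
- first term: 1.960 × √0.46355 = 1.334
- second term: 0.8416 × √0.4271 = 0.550
- n = (1.334 + 0.550)² / 0.27² = 48.7, rounded up to 49

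This matches the stated 49 + 49. The allowance is 120 − 98 = 22 patients, and 22/120 = 18.3%.

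**Step 3. Illustration of the share of events affected**

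The documents give no event rate and no relative risk in dropouts, so this is illustration only. Suppose all 22 lacked visit 5, and let m be their risk relative to the 98 completers. The share of cardiac and thromboembolic events falling in patients without visit 5 is

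share = 22m / (98 + 22m)

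| m (assumed) | Calculation | Share |
|---|---|---|
| 1 | 22/120 | 18% |
| 2 | 44/142 | 31% |
| 3 | 66/164 | 40% |

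The base rate cancels, so the shares do not depend on it. They say where events would fall if the allowance were fully used. They are not an estimate of events lost, because some may be captured by procedures not shown.

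**The case against.** The strongest reply is that a journal article condenses the protocol. Serious-event reporting, handling of deaths and procedures at withdrawal are commonly left to the full document, which is not shown. This stands, and nothing here claims that such reporting is absent. It does not settle the point, because the article positively names the instrument, the visits and the visit 5 trigger. Even with serious-event reporting elsewhere, non-serious events outside the questionnaire would wait for an open question until month 8.

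A reader might go further and infer that records of patients who die or drop out are not searched, so that their events are missed. The documents do not support that. No sentence restricts the search to attenders, and it could be run for everyone. Patients who leave early also contribute questionnaire data up to their last visit.

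A reader might also infer that the safety conclusion would rest on survivors' recall. For cardiac and thromboembolic events in attenders this is wrong, since the answer is checked against the medical record. Reliance on recall is limited to other event types that the questionnaire does not list.

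Three further replies have some weight.

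- The 22 is a sample-size allowance, not a prediction of missing safety follow-up. Patients whose oxaliplatin is reduced or stopped early stay in the trial and may still attend visit 5.
- The questionnaire does collect several common symptoms prospectively, such as nausea and vomiting, diarrhea and fatigue.
- Safety is not among the listed aims, and outcomes other than the primary are called exploratory. That lowers the stakes, but the plan still sets out to document these events.

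**Conclusion.** The point holds in a limited form. As the article is written, the adverse-event tool at visits 2 to 4 is a quality-of-life form that cannot record bleeding, infection, allergy, rash, or cardiac or thromboembolic events, and the only open-ended question is at 8 months. For cardiac and thromboembolic events, patients who do not reach visit 5 have no stated route of capture.

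The size cannot be estimated from the documents. The allowance of 22 of 120 (18%) is an upper-range illustration of how many could lack visit 5, and the 18% to 40% share of events rests wholly on assumed relative risks of 1 to 3.

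The conclusion assumes that the article states the procedure as it will be followed and that the full protocol does not replace it. The primary endpoint and the sample size are unaffected. The change is worth making because the stated method makes safety data depend on attendance, and the remedy is cheap.

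**What to change.** 1. Ask the same open-ended adverse-event question, recording onset date, at visits 2, 3, 4 and 5 and at the two phone calls.
2. Keep the QLQ-C30 as a quality-of-life outcome and stop naming it as the adverse-event tool.
3. State that the cardiac and thromboembolic record search, with its existing terms, is run over the trial period for every randomised patient, regardless of visit 5 attendance or the patient's answer, as far as consent allows. What the consent permits after withdrawal cannot be seen in the article and should be checked.
4. If the full protocol already has serious-event reporting that covers deaths and withdrawals, refer to it in these two sections.

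The cost is a few minutes at contacts that already take place and a small number of extra searches: at most about 22 if the allowance were fully used and consent permitted. No visit or sample size changes. The article reports 15 of 120 patients included at the time of writing. The search can be applied retrospectively to all of them, whereas the open question helps only at contacts still to come.
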